### Statistical analysis

SPSS (V.22.0; SPSS, Inc) and GraphPad Prism (V.8, GraphPad software Inc, San Diego, California, USA) will be used for data processing and analyses. Categorical variables will be expressed as numbers and frequencies, and between-group differences will be evaluated with Fisher’s exact test. Continuous variables will be expressed as the mean±SD. The Kolmogorov-Smirnov test will be used to determine whether continuous variables are normally distributed. The Student’s t-test will be used for normally distributed data, and the Wilcoxon signed-rank test will be used for non-normally distributed data. All statistical tests will be two-sided with p<0.05 considered statistically significant.

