**Methods and analysis:**

This single-centre, single-blind, prospective, randomised clinical trial will include 54 patients with HMMHRD who will first undergo phacoemulsification and intraocular lens implantation and then vitrectomy combined with lens capsule flap transplantation (experimental group) or ILM tamponade (control group). Study participants will be randomly allocated in a 1:1 ratio to experimental and control groups. Follow-up will be conducted 1, 3 and 7 days and 1, 3 and 6 months after surgery in both groups. Necessary examinations will be performed at each follow-up visit. Measurement outcomes include postoperative situation of macular hole closure, best-corrected visual acuity, macular retinal function and macular retinal sensitivity. The primary outcome is type I closure rate of MH 6 months after operation. Intergroup comparisons of the proportions of patients with type I closure of MH will be performed with Fisher’s exact test.

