**Trial registration number:**

ChiCTR2200057836.

Strengths and limitations of this studyThis is the first randomised controlled trial investigating the efficacy and safety of vitrectomy combined with lens capsule flap transplantation in the treatment of high myopia macular hole retinal detachment.In addition to anatomical measurement, functional measurements, including best-corrected visual acuity, macular retinal function and macular retinal sensitivity, are also used to evaluate the postoperative efficacy.Based on whether the macular hole reaches 400 µm, this trial will adopt the stratified randomisation method through the central random system.Strict quality control measures, including adequate concealment of randomised group allocations, will be implemented.Difference in preoperative lens opacity affecting the baseline visual acuity of the two groups and difficult evaluation of vitreoretinal surgery are the limitations of this trial.

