### Randomisation and blinding

The stratified randomisation method will be adopted in allocating participants to the two groups in a 1:1 ratio using the central random system. The stratification factors are as follows: (1) MH size >400 µm and (2) MH size ≤400 µm. Except the surgeon, all researchers, including the outcome assessors, statisticians and data analysts, will be blinded to group assignment, but providers of the intervention/control will be informed by necessity. Vitrectomy combined with lens capsule flap transplantation or ILM tamponade will be performed by one experienced surgeon. Before the trial, researchers will be fully trained in the randomisation procedure and made aware of their individual responsibilities. The successful implementation and maintenance of the randomisation and blinding method will be validated.

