### Primary outcome

The primary outcome is type I closure rate of MH 6 months after operation.

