### Sample size

Although no RCT of lens capsule flap transplantation in the treatment of HMMHRD has been reported, according to the existing published papers^23 29^ related to this study, the type I closure rate in the experimental group was expected to be 96.0%, whereas the rate in the control group was should be 65.0%. An a priori power analysis conducted using a two-tailed test (power=0.8) at the 5% significance level indicated that 21 participants are required in each group. Considering the attrition rate of 20%, the sample size in each group was determined as 27. With the 1:1 allocation, 54 participants will be recruited.

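### Randomisation is stratified by macular hole size, but the primary test is a pooled Fisher's exact test: it leaves the strata unused and, mainly because it is discrete, gives up about 12 to 13 points of power

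*Protocol article*

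**What the plan says.** **Design.** The Randomisation and blinding section of the protocol article states: "The stratified randomisation method will be adopted in allocating participants to the two groups in a 1:1 ratio using the central random system". Only one factor is used, MH size, above 400 µm or not. The list of strengths and limitations presents this as a strength: "this trial will adopt the stratified randomisation method through the central random system".

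**Primary outcome.** The section of that name defines it: "The primary outcome is type I closure rate of MH 6 months after operation". For each patient this is a yes/no result.

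**Primary test.** It is fixed twice. The Abstract says: "Intergroup comparisons of the proportions of patients with type I closure of MH will be performed with Fisher’s exact test". The Statistical analysis section applies the same test to every categorical variable: "Categorical variables will be expressed as numbers and frequencies, and between-group differences will be evaluated with Fisher’s exact test". Neither place mentions the strata, and the article describes no stratified or adjusted analysis.

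**Planning rates.** The Sample size section gives one rate for each arm. On the new operation it says "the type I closure rate in the experimental group was expected to be 96.0" per cent. On the comparator it says "whereas the rate in the control group was should be 65.0" per cent. With a two-sided 5% level and power 0.8, this gives 21 per group, raised to 27 for 20% attrition.

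**The concern.** A factor chosen for stratified randomisation normally enters the primary analysis. If it predicts outcome, stratification removes part of the chance variation between arms. A pooled test does not know this and overstates the variance of the comparison. Fisher's exact test has its own conservatism as well: with few patients per arm and a rate near 100%, the attainable p-values are coarse and the actual error rate falls well below the nominal 5%.

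At stake are the power of a small single-centre trial on its primary outcome, and an effect estimate that takes no account of the one factor the design singles out. The two sources of loss must be measured separately, because they differ greatly in size.

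**Working it through.** **1. The plan's own figure.** Inputs: 0.96, 0.65, two-sided 0.05, power 0.80 (Sample size section).

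- Arcsine: h = 2·asin√0.96 − 2·asin√0.65 = 0.8634; n = 2(1.960 + 0.842)²/h² = 15.70/0.7454 = 21.06.
- Unpooled normal: n = 7.849 × (0.96×0.04 + 0.65×0.35)/0.31² = 7.849 × 0.2659/0.0961 = 21.7.
- Attrition: 21/0.8 = 26.25, so 27 per arm and 54 in total.

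The stated 21 is therefore reproduced by a large-sample approximation, not by a calculation for Fisher's test.

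**2. Exact power of the planned test.** Power = Σᵢ Σⱼ Bin(i; n, 0.96) · Bin(j; n, 0.65) · 1[Fisher p < 0.05].

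- n = 21: 0.676. n = 27: 0.765. n = 28: 0.790. n = 29: 0.812, the first size above 0.80.
- Actual type I error with both arms at 65%: 0.021 (n = 21) and 0.026 (n = 27).

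**3. Separating the two sources of loss.** Three tests are compared: Fisher, a pooled chi-square (which also ignores the strata), and CMH. The step from Fisher to chi-square isolates discreteness. The step from chi-square to CMH isolates the strata. The CMH statistic without continuity correction is [Σₛ(aₛ − E(aₛ))]² / ΣₛVₛ, with Vₛ = n₁ₛn₀ₛmₛ(Nₛ − mₛ)/[Nₛ²(Nₛ − 1)]. Here aₛ is the number of closures in the experimental arm of stratum s, and mₛ is the total number of closures in that stratum.

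Assumptions not in the protocol: strata of 11+10 or 14+13 patients per arm, and the stratum rates in the table (small/large hole), which average close to 96% and 65%. All results are by exact enumeration.

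| Per arm | Control; experimental | Fisher | Pooled chi-square | CMH | CMH with continuity correction |
|---|---|---|---|---|---|
| 21 | 65/65; 96/96 | 0.676 | 0.792 | 0.792 | 0.579 |
| 21 | 80/50; 99/93 | 0.672 | 0.792 | 0.800 | 0.609 |
| 21 | 90/40; 99.5/92.5 | 0.673 | 0.798 | 0.824 | 0.664 |
| 27 | 65/65; 96/96 | 0.765 | 0.895 | 0.886 | 0.766 |
| 27 | 80/50; 99/93 | 0.764 | 0.898 | 0.899 | 0.785 |
| 27 | 90/40; 99.5/92.5 | 0.772 | 0.907 | 0.917 | 0.827 |

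Fisher to chi-square gains 11.6 to 13.5 points. Chi-square to CMH changes power by 0.0, +0.8 and +2.6 points at 21 per arm, and by −0.9, +0.1 and +1.0 at 27.

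**4. Type I error, both arms at the control rates.**

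| Per arm | Null | Fisher | Pooled chi-square | CMH |
|---|---|---|---|---|
| 21 | 65/65 | 0.021 | 0.054 | 0.047 |
| 21 | 80/50 | 0.016 | 0.043 | 0.050 |
| 21 | 90/40 | 0.007 | 0.025 | 0.048 |
| 27 | 65/65 | 0.026 | 0.051 | 0.050 |
| 27 | 80/50 | 0.019 | 0.040 | 0.050 |
| 27 | 90/40 | 0.009 | 0.023 | 0.047 |

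Ignoring a prognostic stratum pushes a pooled test's error further below 5%. CMH stays near 5%.

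**5. Wider assumptions.** Simulation (20,000 runs per setting) with 30% to 70% of patients in the large-hole stratum and a hole-size odds ratio of 1 to 9 gives CMH power of 0.79 to 0.84 at 21 per arm and 0.88 to 0.93 at 27, with type I error of 0.043 to 0.054. A stratified exact test reaches only 0.65 to 0.73 at 21 per arm.

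**The case against.** **The strata contribute little.** This stands. A reader might infer that leaving the strata out is what makes the test conservative, and so attribute the whole gap (for example 0.76 v 0.90 at 27 per arm) to it. The figures do not support that: a pooled chi-square, which also ignores the strata, recovers almost all of the gap.

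**The power shortfall is really a sample-size problem.** Largely true. The 21 per group comes from an approximation that does not describe Fisher's test. One choice of primary test settles both matters, but the loss should be counted only once.

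**Fisher's test is valid and defensible with so few patients.** Also true. Ignoring the strata does not raise the type I error, so nobody should read this as an invalid analysis.

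**The protocol never says that hole size predicts closure.** Correct. It names the factor and gives neither the stratum shares nor closure rates by size. The stratum-level results are therefore conditional on assumptions.

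**CMH is a large-sample test in sparse tables.** At 99%/93% with 11+10 per arm, only about 0.1 and 0.7 failures are expected in the experimental strata. The worry is fair, but enumeration shows the error held at about 0.047 to 0.050 under nulls averaging close to 65%.

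**An analysis plan may add a stratified analysis.** It may, and covariates for the functional outcomes can be left to it. But the article names Fisher's test for type I closure in two places, so the primary test is a stated choice and not a gap.

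**Conclusion.** The point holds as one of efficiency. The primary test does not follow the stratified design, and at the planned rates it has power of about 0.68 at 21 per arm and 0.76 at 27, below the stated 0.80 even with no attrition. Its actual type I error is about 0.01 to 0.03 under null rates averaging 65%.

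About 12 to 13 points of power are lost to the discreteness of Fisher's test. The strata account for about −1 to +3 points, with the upper end reached only if hole size is strongly prognostic. The Fisher power figures rest on the protocol's own rates. The split by strata rests on assumed shares and stratum rates.

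The strata still favour CMH over a pooled chi-square. The pooled chi-square's error drifts with the prognostic strength of hole size (0.051 down to 0.023 at 27 per arm), while CMH stays close to nominal and matches the randomisation.

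**What to change.** Before the first patient is enrolled (Trial status describes the trial as still in preparation), amend the Abstract and the Statistical analysis section as follows:

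- The primary test of type I closure at 6 months is a two-sided CMH test stratified by MH size as randomised, **without continuity correction**. This detail decides whether the change helps: with the correction, power at 21 per arm is 0.58 to 0.66, below Fisher's 0.67 to 0.68. Confirm which statistic the chosen software prints.
- The effect estimate is the Mantel-Haenszel risk difference with its 95% CI.
- Fisher's exact test is kept as a sensitivity analysis and is not a second route to significance.

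On the assumptions shown, this brings power to about 0.79 to 0.82 at 21 per arm and 0.89 to 0.92 at 27.

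The cost is a short amendment. No extra patients or data are needed, because the stratum is recorded at randomisation. The price is reliance on an asymptotic test in sparse tables, so the amendment should cite the enumerated error rates. If the team prefers to keep Fisher's test as primary, it should state the true power and note that 29 evaluable patients per arm are needed to pass 0.80.

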The key to the treatment of HMMHRD is to restore the normal anatomical structure of the macular region, improve the continuous traction state of the vitreous to the retina and induce retinal reattachment. The main surgical procedures include extrascleral surgery (scleral buckling, macular banding and posterior scleral reinforcement), intraocular surgery (vitrectomy) and combined intraocular and extraocular surgery. Currently, vitreoretinal surgery is the mainstream surgical method for the treatment of HMMHRD. Among them, pars plana vitrectomy (PPV) can relieve the mechanical traction of the vitreous cortex on the macula, restore the anatomical structure, effectively reduce retinal oedema and facilitate fluid exchange, and promote the recovery of retinal function in the macular region. It is one of the most routinely performed operations.^13^ However, the abnormalities of the anatomical structure in high myopia, such as long ocular axis, retinal choroidal atrophy at the posterior pole, posterior scleral staphyloma and ‘macular white hole’, lead to increased surgical difficulty, resulting in low retinal reduction and hole closure rate and high recurrence rate in patients with HMMHRD after simple vitrectomy. In addition, scar healing, retinal interlayer structure disorder, RPE atrophy and ganglion cell damage occur in MHs after operation, which lead to unsatisfactory visual function recovery, even if retinal anatomical reduction was achieved.^14 15^ Therefore, to improve the success rate of surgery and preserve the visual function of patients as much as possible, combined macular interface surgery is needed after vitrectomy removes the traction of the vitreous to the macula. The combination of surgical methods, such as ILM peeling, ILM flap and ILM tamponade, are currently in practice. Improving the visual function of patients based on improving the reduction rate is the key to the selection of macular interface surgery for HMMHRD.^16 17^

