Although these operations can improve the healing rate of MH, obtaining the ILM tissue at the edge in patients with high myopia remains challenging. The challenge is due to the problems of posterior scleral staphyloma, retinal choroidal atrophy and difficulty in identifying the ILM.^18 19^ Moreover, because the ILM is originally soft, under the influence of the long axis of high myopia, ILM softens further under traction. Therefore, moving the ILM to a suitable position to prevent displacement is difficult.^19 20^ As a result, the role of improving visual function postsurgery remains controversial. Therefore, the choice of operation mode of macular interface is particularly important.

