### Interventions

All participants who meet the inclusion criteria of this study and do not meet any of the exclusion criteria can be included in this study. Before the surgery, the patients should receive complete preoperative ophthalmic examination, including best corrected visual acuity (BCVA), slit lamp inspection, axial length, presence of staphyloma, myopia dioptres, intraocular pressure (IOP), ocular B-ultrasound, OCT, multifocal electrophysiology (mfERG), MP-1 microperimeter, fluorescence fundus angiography and indocyanine green angiography. After passing the screening, the participants who provided written informed consent will be randomly assigned to two parallel trial groups in a 1:1 ratio according to the central randomisation system. The patients will undergo vitrectomy combined with lens capsule flap transplantation or ILM tamponade and regular postsurgery follow-up. Participants will be blinded to the specific surgical methods. The timeline of data collection is shown in table 1.

**Table 1 T1:** Outcome measurements and data collection at each follow-up timepoint

Phase		Screen	Preoperative examination	Postoperative follow-up					
Follow-up		1	2	3	4	5	6	7	14
Time points		Within 1 week before operation	One day before operation	1 day after operation	3 days after operation	7 days after operation	1 month after operation	3 months after operation	6 months after operation
Informed consent		●							
Inclusion and exclusion criteria		●							
Withdrawal criteria			●	●	●	●	●	●	●
Medical history collection		●							
Ophthalmic examination	BCVA	●	●	●	●	●	●	●	●
	Slit lamp inspection	●	●	●	●	●	●	●	●
	Axial length	●						●	●
	Presence of staphyloma	●						●	●
	Myopia dioptres	●						●	●
	IOP	●	●	●	●	●	●	●	●
	Ocular B-ultrasound	●	●	●	●	●	●	●	●
	OCT	●	●	●	●	●	●	●	●
	mfERG	●						●	●
	MP-1 microperimeter	●						●	●
	FFA and ICGA	●							●
Systemic	Vital signs	●	●	●	●	●	●	●	●
examination	Physical examination	●							●
Laboratory examination	routine blood test	●	●				●		●
	Blood biochemistry	●					●		●
	Coagulation function	●							●
	Urinalysis	●							●
	Immune and infection measurements	●				●	●		●
	ECG	●							●
	Chest CT	●							●
Adverse events recorded		●	●	●	●	●	●	●	●

BCVA, best corrected visual acuity; IOP, intraocular pressure; OCT, optical coherence tomography; mfERG, multifocal electrophysiology; FFA, fluorescence fundus angiography; ICGA, indocyanine green angiography.

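### The primary closure comparison is an unadjusted Fisher test that leaves power unused: most of the loss is the test's conservatism, and a smaller, uncertain part is the unused axial length and staphyloma data

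*Protocol article*

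**What the plan says.** - **Test.** Statistical analysis: "Categorical variables will be expressed as numbers and frequencies, and between-group differences will be evaluated with Fisher"'s exact test. The Abstract assigns this test to type I closure by name, so the choice is fixed in the article and not left to a later plan. No covariate is mentioned.
- **Features linked to outcome.** The Introduction attributes low hole closure after simple vitrectomy to "the abnormalities of the anatomical structure in high myopia, such as long ocular axis, retinal choroidal atrophy at the posterior pole, posterior scleral staphyloma" and related changes. It then explains why ILM tissue is hard to obtain in these eyes: "The challenge is due to the problems of posterior scleral staphyloma, retinal choroidal atrophy and difficulty in identifying the ILM". It adds that a long axis makes the ILM softer and harder to place.
- **Data collected.** The Interventions section lists "slit lamp inspection, axial length, presence of staphyloma, myopia dioptres" among the preoperative examinations, and Table 1 places axial length and staphyloma at screening.
- **Randomisation.** The Randomisation and blinding section stratifies on hole size (above 400 µm or not) and on nothing else.
- **Sample size.** The planning rates are 96% closure with the capsule flap and 65% with ILM tamponade. The calculation is reported in these words: "An a priori power analysis conducted using a two-tailed test (power=0.8) at the 5% significance level indicated that 21 participants are required in each group". Allowing for a 20% loss, the section then raises the figure to 27 per arm.

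**The concern.** The protocol names two eye features as obstacles to closure or to the control technique and measures both before surgery. It then compares the arms with a test that can use neither. In a trial of 54 eyes two things are at stake. The first is power, because Fisher's test on a table this small works well below its nominal 5% level. The second is precision, because chance differences between arms in staphyloma or axial length stay in the closure difference as noise. The article's Trial status section calls the study preparatory. Covariates chosen after outcomes are known would not be credible, so the choice has to be made in advance.

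**Working it through.** **1. The plan's own figure.** Inputs from the Sample size section: 0.96 v 0.65, two-sided 5%, power 0.80, 20% attrition.

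Arcsine formula: h = 2·asin√0.96 − 2·asin√0.65 = 2.739 − 1.875 = 0.863, and n = 2·((1.960 + 0.842)/0.863)² = 21.06. The unpooled normal formula gives (1.960 + 0.842)² × (0.96×0.04 + 0.65×0.35)/0.31² = 21.7. The stated 21 is therefore reproduced by an approximate formula. Attrition: 21/0.8 = 26.25, rounded up to 27, as stated.

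**2. Power of the test actually named.** Sum Bin(a; n, 0.96) × Bin(b; n, 0.65) over all tables with a two-sided Fisher p-value of at most 0.05. Exact power is 0.676 at n = 21 and 0.765 at n = 27. With 80.5% closure in both arms (the mean of 96 and 65), the true type I error is 2.3% and 1.9%.

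**3. How much of the shortfall is conservatism alone?** Boschloo's test also uses only the 2×2 table, with no covariate. By enumeration its power is 0.766 and 0.856, with maximum type I error 4.8% and 4.5%. That is 9 points above Fisher at either size.

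**4. Adding the covariates.** The test simulated takes residuals from an arm-blind Firth logistic model and permutes arm within hole-size stratum. The article gives no prognostic strengths, so these are assumed: odds ratio for non-closure 1.5-2 per SD of axial length, 2-3 for staphyloma at 50% prevalence, and 1.5 for the hole-size stratum. Simulated rows are ranges over repeated runs. With 1,500 trials per setting, the standard error is about √(0.78×0.22/1500) = 0.011.

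| Test | 21 per arm | 27 per arm |
|---|---|---|
| Fisher, exact | 0.676 | 0.765 |
| Boschloo, exact | 0.766 | 0.856 |
| Stratified by hole size only, simulated | 0.64-0.69 | 0.77-0.80 |
| Adjusted permutation, uninformative covariates | 0.73-0.76 | 0.86 |
| Adjusted permutation, assumed odds ratios | 0.76-0.81 | 0.87-0.90 |

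The simulated type I error of the adjusted test was 4.5-5.3%.

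Total gain over Fisher: about 8-13 points. Gain with worthless covariates: about 6-10 points (for example 0.76 − 0.676 = 8 points at 21, and 0.86 − 0.765 = 9.5 at 27). What remains for the covariates is about 0-7 points.

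**5. Like-for-like check.** Logistic score tests without and with the two covariates remove the Fisher effect:

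| Odds ratios (axial length per SD, staphyloma) | 21 per arm | 27 per arm |
|---|---|---|
| 1.5 and 2 | 78.8% to 79.5% | 89.7% to 89.3% |
| 2 and 3 | 79.7% to 81.6% | 89.8% to 90.6% |
| 3 and 5 | 79.4% to 85.7% | 89.9% to 93.1% |

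The covariates become worth several points only if they are strongly prognostic.

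**6. Chance imbalance.** With two independent Bin(27, 0.5) counts, the probability of a staphyloma difference of at least 15 points is 22%. If closure differed by an assumed 30 points with staphyloma, such an imbalance would move the closure difference by 0.15 × 30 = 4.5 points.

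**7. Sparse failures.** Expected failures are n × (0.04 + 0.35) = 8.2 at 21 per arm and 10.5 at 27. The chance of none in the experimental arm is 0.96²¹ = 42% and 0.96²⁷ = 33%. In that case ordinary logistic regression with an arm term has no finite treatment estimate. This is why the proposed model is penalised and leaves arm out.

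**The case against.** The strongest objection concerns cause. A reader might infer that 8-13 points of power are lost because axial length and staphyloma are ignored. The figures do not support that. An unadjusted 2×2 test already recovers about 9 points, and the adjusted test gains nearly as much with uninformative covariates. The document gives no odds ratio, no staphyloma prevalence and no closure rate by feature, so no power figure for the covariates can be read from it. This objection stands and limits the point.

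A reader might also infer that uncorrected chance imbalance biases the result or invalidates the test. It does neither. Under randomisation such imbalance is already allowed for in the p-value, and Fisher errs on the cautious side. Adjustment buys precision only.

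Third, the prognostic premise is weaker than it first looks. The statement about low closure concerns simple vitrectomy, which neither arm receives. The remarks on ILM handling bear on the control technique and do not establish a common effect in both arms. Eligibility also narrows the range of eyes, because pathological myopia and macular atrophy are excluded. This stands as a reason to expect the lower part of the 0-7 range. It does not remove the case for using data already on file.

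Fourth, the weak showing of a test stratified by hole size does not prove that the other covariates are what matters, because that test is also affected by discreteness.

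Finally, adjusted analyses are often left to an analysis plan that is not shown. That would cover supportive analyses. It does not alter the primary test, which the article names.

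**Conclusion.** The point holds as one of efficiency. The named primary test has exact power 0.676 at 21 per arm and 0.765 at 27 for the planned 96% v 65%, so it falls short of the intended 0.80 even with no attrition. An adjusted permutation test at about the nominal 5% error gains about 8-13 points under the odds ratios assumed above. Most of that, about 6-10 points, comes from leaving a test whose true error is near 2%. The covariates contribute about 0-7 points, depending on a prognostic strength that the document does not give. The planned analysis is valid, and nothing here implies bias.

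**What to change.** Before enrolment, pre-specify the primary analysis as follows:

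1. Fit a Firth logistic model for month-6 type I closure, without arm, on screening axial length (continuous), staphyloma (yes/no) and hole-size stratum.
2. Compare the residuals between arms with a two-sided permutation test that permutes arm within hole-size stratum. The p-value remains valid if the covariate model is wrong or an arm has no failures.
3. Report the risk difference with a named 95% confidence interval method that still works when an arm has no failures, for example a Miettinen-Nurminen score interval. The permutation argument covers the p-value and not this interval.
4. Keep Fisher's test as a supportive analysis.

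Cost: one analysis paragraph and a short script, with no extra patients or data. The SPSS and Prism menus do not offer this test, so other software is needed, and it is less familiar to readers than Fisher's. If the sponsor prefers a plain 2×2 test, Boschloo's recovers most of the gain (0.766 and 0.856) but does nothing about chance imbalance.

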### Secondary outcomes

The following indicators will be used to comprehensively assess anatomical outcome: (1) type I closure rate of MH 3 months after operation; (2) type II closure rate of MH 6 months after operation; and (3) type II closure rate of MH 3 months after operation.

Functional outcomes will be assessed as follows: (1) changes in BCVA 3 and 6 months after operation compared with baseline; (2) changes in P1 wave response density in the macular region 3 and 6 months after operation compared with baseline; and (3) changes in macular retinal sensitivity 3 and 6 months after operation compared with baseline.

Furthermore, the number of adverse events and reactions, abnormality of ophthalmic examination, abnormal systemic symptoms and laboratory results will be recorded at each follow-up visit.

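### A weak Kolmogorov-Smirnov pre-test picks the test for each secondary functional outcome, and its non-normal branch names a paired test that cannot compare the two arms

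*Protocol article*

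**What the plan says.** The Statistical analysis section of the protocol article gives a two-stage rule for continuous variables. First, "The Kolmogorov-Smirnov test will be used to determine whether continuous variables are normally distributed". Then Student's "t-test will be used for normally distributed data", and "the Wilcoxon signed-rank test will be used for non-normally distributed data". The significance rule is "All statistical tests will be two-sided with p<0.05 considered statistically significant". The section does not say whether the Lilliefors correction applies, what level the pre-test uses, or whether it is run per arm, pooled or on residuals.

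The continuous efficacy variables are listed under Secondary outcomes. The first is "changes in BCVA 3 and 6 months after operation compared with baseline"; P1 wave response density and macular retinal sensitivity are defined in the same way. That makes three outcomes at two visits, or six between-group comparisons. The primary outcome, type I closure at 6 months, is binary and is compared with Fisher's exact test.

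On numbers, the Sample size section says that the power analysis "indicated that 21 participants are required in each group", and then: "Considering the attrition rate of 20%, the sample size in each group was determined as 27".

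**The concern.** Two things look wrong in this rule.

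- **The choice of test depends on the data.** It is made by a normality test that detects little at this sample size. The same outcome can be analysed by a t-test at 3 months and a rank test at 6 months, for reasons that are largely chance.
- **The fallback is the wrong kind of test.** The signed-rank test needs pairs or a single sample. Participants in the two arms are independent and no pairing is defined. Applied within each arm against baseline, it tests change in that arm and says nothing about the difference between arms.

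A third matter is efficiency. Baseline is used only through subtraction, although it is collected for all three measures (Table 1).

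At stake is how firmly the trial can speak on functional recovery, which is part of its stated hypothesis and objective. Closure is not touched.

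**Working it through.** **Sample size range.** The plan's inflation reproduces: 21 / (1 − 0.20) = 26.25, rounded up to 27 per arm, and 2 × 27 = 54. The functional comparisons therefore rest on about 21 to 27 participants per arm.

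**Assumptions.** The documents give no SD, effect size, distribution shape or baseline correlation for any functional outcome, so all of these are assumed. Simulation: 20,000 trials per cell, pre-test at 5% in each arm, switch to the non-parametric test if either arm rejects, shift of 0.8 SD.

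**Step 1: how often the pre-test detects non-normality.**

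- Lilliefors version, single arm, n = 21: 35% (lognormal, σ = 0.5), 60% (exponential), 26% (t with 3 df). At n = 27: 45%, 74% and 32%.
- Uncorrected version, either arm, n = 21: 3%, 9% and 6 to 7% for the same shapes, so the t-test is nearly always used.
- Truly normal data: the Lilliefors version still switches test in about 10% of trials.

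**Step 2: different tests at the two visits.** With an assumed between-visit correlation of 0.5 to 0.9 and n = 21, the Lilliefors version picks different tests at 3 and 6 months in 33 to 48% of trials for t3 data, 34 to 47% for lognormal (σ = 0.5) and 16 to 18% for normal data. Uncorrected Kolmogorov-Smirnov does so in 5 to 12% for the non-normal shapes.

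**Step 3: type I error.** With a rank-sum fallback, the two-stage rule rejects in 4.5 to 5.5% of null trials in every cell, for both versions and both sample sizes. Among trials that pass the Lilliefors pre-test, the t-test error is higher: 6 to 7% for lognormal (σ = 0.5) and exponential data at n = 21, up to 9% at n = 27, and 11 to 12% for strong lognormal (σ = 1).

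**Step 4: power (%) at n = 21 per arm, shift 0.8 SD.**

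| Shape | Fixed t | Fixed rank-sum | Lilliefors, then rank-sum | Uncorrected K-S, then rank-sum | Lilliefors, then signed-rank on arbitrary pairs |
|---|---|---|---|---|---|
| Normal | 71.3 | 68.6 | 71.0 | 71.3 | 70.8 |
| Uniform | 71.6 | 65.0 | 70.6 | 71.6 | 70.5 |
| Lognormal, σ = 0.5 | 73.2 | 84.8 | 82.7 | 74.4 | 76.5 |
| Lognormal, σ = 1 | 79.4 | 98.8 | 98.7 | 92.2 | 92.2 |
| Exponential | 72.7 | 89.6 | 88.5 | 75.3 | 77.8 |
| t, 3 df | 78.1 | 90.9 | 88.2 | 81.1 | 83.6 |
| Contaminated normal | 74.3 | 91.1 | 88.6 | 77.0 | 82.4 |

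Loss against a fixed rank-sum test over the five skewed or heavy-tailed shapes:

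- Lilliefors, then rank-sum: from 98.8 − 98.7 = 0.1 to 90.9 − 88.2 = 2.7 points.
- Uncorrected, then rank-sum: from 98.8 − 92.2 = 6.6 to 89.6 − 75.3 = 14.3 points.
- Lilliefors, then signed-rank on arbitrary pairs: from 98.8 − 92.2 = 6.6 to 89.6 − 77.8 = 11.8 points.

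A smaller run (2,000 trials, t3 data, shifts of 0.8 and 1.0 raw units, i.e. 0.8/√3 = 0.46 and 1.0/√3 = 0.58 SD) gave Lilliefors losses of 50.6 − 47.4 = 3.2 and 69.8 − 66.4 = 3.4 points. Hence the range of 0 to 4. The uncorrected losses there were 50.6 − 42.4 = 8.2 and 69.8 − 58.6 = 11.2 points, inside 7 to 14.

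**Step 5: baseline as covariate.** For equal variances and baseline-outcome correlation r, the variance of the adjusted comparison relative to raw change is (1 − r²) / [2(1 − r)] = (1 + r)/2. The reduction is (1 − r)/2: 15% at r = 0.7 and 35% at r = 0.3.

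**The case against.** - **The rule is stated in advance, and it controls error.** This stands. Only the branch is left to the data, and overall type I error stays near 5% with a valid fallback. A reader might infer a false-positive problem; the calculations do not support one. The higher conditional error in step 3 averages out across branches.
- **The power loss is not general.** This stands. A reader might infer that the rule always loses power on non-normal data. With Lilliefors and a rank-sum fallback the loss is small, and against a fixed t-test that rule gains 9.5 to 19.3 points on the five skewed or heavy-tailed shapes. On normal and uniform data it beats a fixed rank-sum test (71.0 v 68.6 and 70.6 v 65.0). The larger loss needs the uncorrected version, which the article neither names nor excludes.
- **Baseline is not ignored.** This stands. Change scores use it by subtraction. The point is efficiency, and taken alone an article could leave covariates to an analysis plan. It matters here because a stated rule has to be replaced anyway.
- **"Signed-rank" may be a slip for rank-sum, or meant for within-arm change.** Possibly, but the text names no other non-parametric test for continuous variables, so the between-group comparison has no valid one. In the simulation, arbitrary pairing of equal arms kept type I error near 5%. The objection to it is that the answer depends on a meaningless pairing, needs equal numbers per arm, and wastes power.
- **The linear model is not always the stronger test.** This stands. For t3 data (n = 21 per arm, assumed shift 0.6 SD of change), power at r = 0.3, 0.5, 0.7 and 0.9 was 76, 67, 64 and 59% for the model, against 67, 67, 68 and 72% for the rank-sum test of change.

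**Conclusion.** The concern holds as a minor point confined to secondary outcomes. The plainest error is the signed-rank test: it is paired and is not valid for comparing two independent arms. The Kolmogorov-Smirnov step is a weak selector at 21 to 27 per arm. Uncorrected, it seldom triggers except under strong skew; with Lilliefors, it can assign different tests to one outcome at its two visits in a third to a half of trials for moderately skewed or heavy-tailed data.

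The cost in power is conditional: about 0 to 4 points against a fixed rank-sum test with Lilliefors and a valid fallback, and about 7 to 14 points with the uncorrected version, on skewed or heavy-tailed data. The 15 to 35% variance reduction from covariate adjustment applies to roughly normal data with r between 0.7 and 0.3. Shapes, shifts and correlations are all assumptions, because the documents give none. Nothing here bears on the primary closure comparison.

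**What to change.** Delete the Kolmogorov-Smirnov step. For every functional outcome and visit, pre-specify a linear model of the follow-up value on arm, baseline value and hole-size stratum (>400 v ≤400 µm, the randomisation factor). Name a Mann-Whitney (rank-sum) test of change as the fixed sensitivity analysis, replacing the signed-rank test for between-group comparisons.

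The cost is two sentences of analysis text. The baseline values and the stratum are already collected, and both methods are in the named software. The trade-off is some loss of power against the rank test if data are heavy-tailed and the baseline correlation is high; the fixed sensitivity analysis is there to show whether that matters. The article describes the trial as still in preparation, so the change could be made before any outcome data exist.
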